**Methods:**

Ten kindergartens will be randomly selected to implement DBED, while ten will act as controls, offering ordinary parent-teacher conferences. Parents of at least 100 + 100 children will be recruited. The primary outcome will be children’s mental health in the intervention group as assessed by the Strengths and Difficulties Questionnaire (SDQ), during the 5-year follow-up, compared to the control group. Secondary outcomes will be (i) the effect of DBED on parental stress as measured by the Parental Stress Scale (PSS) and (ii) time to activation of support, as measured by the duration from the first parent-teacher conference to activation of any support, comparing the two groups. We will also assess (iii) socio-demographic predictors for mental health development, parent and teacher concern for the child, parental stress, and parent satisfaction with DBED, (iv) screening properties of DBED compared to SDQ, and (v) social validity of DBED as measured by user-satisfaction questionnaires and interviews with both parents and teachers.

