### Objectives {7}

The primary objective is to evaluate DBED’s impact on mental health for children in kindergarten measured by the Strength and Difficulties Questionnaire (SDQ) scores. However, for a better understanding of potential mechanisms, secondary objectives are to evaluate how DBED influences parental stress and activation of interventions for mental health concerns, to establish the screening properties of DBED to detect mental health problems among children in kindergarten, and evaluate its acceptability for kindergarten teachers.

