The factor structure of EWQ as reported by parents and teacher, respectively, prior to the parent-teacher conference and as reported DBED concluded concern from the parent-teacher conference, primarily at baseline, but also at the following half-year registrations for comparative reasons.Agreement between (i) reported concern and DBED concluded concern, respectively, measured by total EWQ score and EWQ sub-scores, and (ii) mental health measured by SDQ Total difficulties score, each sub-scale score, and two SDQ impact scores, respectively, at baseline.Agreement between parent’s and teacher’s mental health report measured by agreement between parent and teacher SDQ scores and the above mentioned SDQ impact scores at baseline and after 12, 24, and 36 months, respectively.Agreement between parents and teacher in possible concerns for the child measured by percentage of EWQ items rated as the three different response options, respectively (satisfied; a bit uncertain; concerned), at baseline and after 12, 24, and 36 months, respectively).Change from reported to concluded concern during the parent-teacher conference measured similarly as the preceding outcome.Satisfaction with the DBED after all parent-teacher conferences measured by the study-specific satisfaction questionnaires for parents and teachers, respectively.Predictors of mental health change during the 5-year follow-up. Mental health is measured by SDQ-scores (Total difficulties score, sub-scales and impact scores) and the predictors (at baseline) are measured by:◦ Parent’s educational level◦ Satisfaction with economic situation◦ Social support◦ Single parenting◦ Close relatives in the vicinity◦ Norwegian language at home?◦ Is Norway parent’s country of origin?◦ Major illness or handicap◦ Level of parental concern◦ Level of teacher concern◦ Level of DBED concluded concern◦ Parent-teacher agreement after the parent-teacher conversation at baseline◦ Level of parental stressPredictors of parental and teacher concern, respectively. Concern is measured by parent and teacher EWQ total score at baseline and changes throughout the 3-year follow-up period in kindergarten, and the predictors are the same as for mental health change.Predictors of parental stress. Parental stress is measured at baseline and changes throughout the total follow-up period of 5 years, and the predictors are the same as for mental health change (except parental stress).Predictors of parent satisfaction. Parent satisfaction is measured by the study-specific satisfaction questionnaire at baseline and changes throughout the 3-year follow-up period in kindergarten, and the predictors are the same as for mental health change.

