Baseline information (demographics, social support, health related information)◦ Parent’s educational level (values 0–3)◦ Satisfaction with economic situation (Visual analogue scale, values 0–10)◦ Social support, adapted from the PIRM study [15] containing nine items. See Additional file 2 for details.◦ Single parenting (values 0–1)◦ Close relatives in the vicinity (values 0–1)◦ Norwegian language at home? (values 0–1)◦ Is Norway parent’s country of origin? (values 0–1)◦ Major illness or handicap (child) (values 0–1)EWQ (only for the intervention group) [10] is a novel tool for assessing parents and kindergarten teachers’ possible concerns for a child. The psychometric properties of EWQ are not yet established but will be subject to analyses in the present study. We will apply the total EWQ score (values 0–74) and EWQ sub-scores (five sub-scores, values from 0–10 to 0–18). EWQ will be scored in two different situations:◦ Prior to the parent-teacher conference, completed by both each parent and teacher.◦ As conclusions after the parent-teacher conference, completed by teacherSDQ, 2–4 years version [16] is a standard screening tool for mental health symptoms among young children with well-established validity [16] and psychometric properties [17]. We will apply SDQ Total Difficulties Scale score (values 0–40), each sub-scale score (values 0–10), and two SDQ impact scores (values 0–3 and 0–12, respectively) addressing difficulties in general and in four different areas of daily functioning.PSS is an 18-item questionnaire (values 0–72) assessing parents’ feelings about their parenting role, exploring both positive aspects (e.g., emotional benefits, personal development) and negative aspects of parenthood (e.g., demands on resources, feelings of stress) [12].User satisfaction with the DBED method (only for the intervention group) measured after all parent-teacher conferences by study-specific questionnaires, see Additional file 2.◦ Parent questionnaire: five items (values 0–15) and optional free text response◦ Teacher questionnaire: seven items (values 0–21) and optional free text responsePossible supportive actions initiated, see Additional file 2.How specific questionnaires relate to the primary, secondary, and process outcomes, respectively, is described in the “Outcomes {12}” section. Collection of qualitative data for process outcomes is described in the “Data management {19}” section.

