## Statistical methods

### Statistical methods for primary and secondary outcomes {20a}

Primary outcome:◦ Possible differences between children in intervention and control kindergartens in mental health trajectories will be estimated by Latent growth curve (LGC) models (gives equal results as linear mixed/multilevel models, given similar parameter specification). Both random intercept fixed slope and random intercept random slope will be analyzed, meaning models with no variance in change (slope) and models with individual differences in slope (random effects). Then the full unstructured matrix with random intercept, random slope, and the covariance between intercept and slope will be tested. Initially, linear change over time will be tested. If not supported with data, different non-linear change models will be explored (quadratic, cubic, piecewise growth). Then, substantial predictors will be entered into the model and analyzed. Also, within level residual structures will be tested.Secondary outcomes:◦ Possible differences between children in intervention and control kindergartens in parental stress and time to initiated locally available supportive action, respectively, will be analyzed in a similar way to the primary outcome.Process measures:◦ Factor structure will be estimated by confirmatory factor analysis (CFA).◦ Agreements between:▪ Reported concern (EWQ) and DBED concluded concern (EWQ), respectively, and mental health (SDQ): correlations (Pearson’s and Spearman), Cohen’s (weighted) Kappa, CFA: uni-, bi-, and tri-factor models representing different sources of information (parent 1, parent 2, teacher. Latent difference score (LDS) models will also be explored for common levels and differences within and between families.Parent’s and teacher’s mental health report (SDQ): correlations (Pearson’s and Spearman), CFA, including method factors, LDS models.Parents’ and teacher’s possible worries for the child: Cross table with chi-quadrat test, Cohen’s weighted Kappa, CFA, and LDS models.▪ Change from reported (EWQ) to concluded concern (EWQ) during the parent-teacher conference: cross table with chi-quadrat test, Cohen’s weighted Kappa, CFA/LDS models.▪ Satisfaction with DBED:Initial: distribution of scores and mean values of each item. Mean value of total score.Follow-up: repeated measures of mean values of each item and total scores and LGC models.▪ Predictors of mental health change, parent concern, teacher concern, parent satisfaction, parental stress: LGC models with predictors (conditional LGC models).Statistical principles◦ Level of statistical significance: We will use the threshold of *p* = 0.05 for the main analysis. However, the threshold perspective has been debated, and there is considerable literature claiming another perspective as a relevant alternative. This implies the use of exact p-values as a degree of certainty of the generalization from sample to population. In the exploratory part of the project, this practice will be used. In addition, we will calculate effect sizes to evaluate the results beyond statistical significance.◦ Adjustment for multiplicity: Detailed power analysis (Monte Carlo analysis) was used to decide sample size for satisfactory power. Adjustment is irrelevant for this analysis. Regarding other statistical analyses, analyses may introduce risk for Type 1 errors when testing family-wise tests. When testing specific hypotheses (see above), no adjustment should be necessary. When exploring differences and relations not pre-specified in hypotheses (family wise tests), Bonferroni corrections will be used.◦ Confidence intervals to be reported: 95%◦ Methods used for assumptions to be checked for statistical methods: Residuals will be saved and checked for normality and homoscedasticity. Relations will be plotted and linearity in relations evaluated.◦ Details of alternative methods to be used if distributional assumptions do not hold: Bootstrapping will be used if normality does not hold. However, larger samples are robust for such deviations.If survival models (Cox and non-proportional parametric hazard models based on Weibull distribution), the proportional assumption will be tested. In addition, covariates will also be tested as time-dependent covariates to explore whether they relate to events differently over time.

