## Discussion

In societies with high preschool uptake, such as Norway, kindergartens have great potential for mental health promotion in young children. Targeted interventions in preschools, where children may require additional support, have been proven to deliver far greater societal returns compared to interventions introduced later in life [4]. We believe that the PRO-DIALOG project holds the potential to generate such an impact and have both short-term and long-term benefits for individuals and society.

To our knowledge, this is the first trial to investigate a systematic parent-teacher conference in kindergartens aiming to promote child mental health. To avoid contamination of the intervention on control cases, a block randomized design was regarded as appropriate. With this design, all teachers to the children of the eligible birth cohorts in the intervention kindergarten receive training in DBED. Likewise, all the eligible parents are informed and invited to participate.

Despite the RCT design, assuming equality between the intervention and control group might be optimistic. However, adjusting for differences by both a multi-variable and multi-level approach will mitigate such a bias.

As far as we know, there is no convention for what a significant difference in mental health level (SDQ Total difficulties score after 3 years) is in a community-based population exposed to a secondary preventive measure. Hence, our power estimation is based on a somewhat uncertain assumption. The recruitment of parents will go on until the minimum number of participants is reached; however, it will not stop before all invited parents have been given the opportunity to consent to participation. So, the number of participants will probably exceed 100 + 100.

Along with the core trial, aspects beyond the long-term outcome of child mental health are addressed, such as screening properties and social validity of this novel method. For further studies of DBED, these process data will be of great interest.

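### The methods listed for EWQ and DBED concluded concern against SDQ measure association and agreement, so they answer the screening objective only in part and give no sensitivity, specificity or predictive values.

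*Protocol article*

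**What the plan says.** **The aim.** Among its secondary objectives, Objectives {7} of the protocol article sets out "to establish the screening properties of DBED to detect mental health problems among children in kindergarten". The Abstract (Methods) lists "screening properties of DBED compared to SDQ". The Discussion returns to aspects beyond the long-term outcome, "such as screening properties and social validity of this novel method".

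**The outcome that serves it.** Outcomes {12} contains no outcome labelled as screening accuracy. The nearest is a process outcome, the agreement of reported concern and of DBED concluded concern (EWQ total and sub-scores) with "mental health measured by SDQ Total difficulties score, each sub-scale score, and two SDQ impact scores, respectively, at baseline".

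**The measures.** In the data collection section {18a} the index measure is a score: "We will apply the total EWQ score (values 0–74) and EWQ sub-scores". SDQ Total difficulties is also a score (0–40). The article gives no cut-off for either.

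**The methods.** For this comparison, Statistical methods {20a} lists "correlations (Pearson’s and Spearman), Cohen’s (weighted) Kappa" and factor models by information source, and adds: "Latent difference score (LDS) models will also be explored for common levels and differences within and between families". Cross tables are listed for parent against teacher concern and for reported against concluded concern, but not for EWQ against SDQ. Sensitivity, specificity, predictive values and ROC analysis appear nowhere in the article.

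**The concern.** Detecting problems is a classification task. The reader wants to know what share of children with problems the method flags, and what share of children without problems it flags as well. A correlation, a kappa or a factor loading reports neither. An analysis that followed the listed methods to the letter would therefore leave the central part of this objective without a figure.

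The false-positive side has particular relevance here. The Introduction reports two criticisms that some users make of existing screening programmes: that they pathologise natural variation, and that they create needless worry about healthy children. Specificity is the statistic that bears most directly on the second, though only relative to SDQ.

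There is a smaller difficulty with kappa. It compares two ratings on one common set of categories. EWQ and SDQ totals have different ranges, and the article states no shared categorisation, so as written the statistic is not defined for this pair.

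**Working it through.** The article states no figure for screening accuracy, so there is nothing to reproduce. The check is whether the listed statistics determine sensitivity and specificity.

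**Inputs from the article.** EWQ total 0–74 (37 items, 37 × 2 = 74). SDQ total 0–40. EWQ collected in the intervention arm only. Minimum of 100 children per arm.

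**Assumptions (not in the article).** SDQ-positive prevalence p = 10%, with 5% to 20% as the range. Correlation r = 0.5, with 0.4 and 0.6 as the range. Kappa = 0.40.

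**1. Does a correlation fix accuracy?** Take both scores as bivariate normal with correlation r. Let q be the share of children flagged and B the probability of being both flagged and SDQ-positive. Then sensitivity = B/p and specificity = 1 − (q − B)/(1 − p). For r = 0.5 and p = 0.10:

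| Flagged q | B | Sensitivity | Specificity |
|---|---|---|---|
| 5% | 0.019 | 0.19 | 0.97 |
| 10% | 0.032 | 0.32 | 0.92 |
| 20% | 0.051 | 0.51 | 0.83 |
| 30% | 0.065 | 0.65 | 0.74 |

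For example, at q = 20%: 1 − (0.20 − 0.051)/0.90 = 0.83. Over the same flag rates, sensitivity runs from 0.16 to 0.58 for r = 0.4 and from 0.24 to 0.74 for r = 0.6. One correlation is compatible with very different screening performance.

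**2. Does kappa fix accuracy?** Suppose both measures are dichotomised. Observed agreement is Po = Se·p + Sp·(1 − p). The share flagged is q = Se·p + (1 − Sp)(1 − p). Chance agreement is Pe = p·q + (1 − p)(1 − q), and kappa = (Po − Pe)/(1 − Pe). At p = 0.10:

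- Se 0.40, Sp 0.959: Po = 0.9031, q = 0.0769, Pe = 0.8385, kappa = 0.0646/0.1615 = 0.40. The positive predictive value is 0.040/0.0769 = 0.52.
- Se 0.90, Sp 0.801: Po = 0.8109, q = 0.2691, Pe = 0.6847, kappa = 0.1262/0.3153 = 0.40. The positive predictive value is 0.090/0.2691 = 0.33.

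The same kappa thus covers a screen that misses 60% of SDQ-positive children and one that misses 10%. The pattern holds across the assumed range: for kappa 0.40 the pairs run from 0.40/0.975 to 0.90/0.887 at 5% prevalence, and from 0.40/0.944 to 0.90/0.678 at 20%.

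**3. Factor and difference models.** These describe common factors and score differences between informants. They involve no threshold and so give no detection rate.

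**4. Precision if accuracy were reported.** With 100 children and p = 10%, about 10 are SDQ-positive. An observed 8/10 has an exact 95% interval of 0.44 to 0.97. With 5, 10, 15 or 20 positives (p = 5% to 20%) and an observed sensitivity of 0.80, Wilson 95% intervals are 0.38–0.96, 0.49–0.94, 0.55–0.93 and 0.58–0.92. All of these treat children as independent and make no allowance for clustering.

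**The case against.** The strongest reply is that the article is internally consistent one level down. The outcome is called agreement, and agreement methods are what it lists. The Abstract's wording about screening properties compared with SDQ can include concurrent agreement. This stands in part: the listed methods do inform the objective. A reader might infer that the objective would go wholly unanswered, but the documents do not support that. What remains is that the Objectives speak of detecting problems, which agreement alone does not establish.

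A second reply concerns kappa. The article does not say it will be computed on raw totals, and listing kappa presupposes some categorisation. A two-category EWQ-by-SDQ table built for kappa would also yield sensitivity and specificity. This stands too. A reader might call kappa meaningless here; it is better called undefined until shared categories are stated. The full protocol or an analysis plan, neither of which is shown, may define cut-offs or add accuracy measures. The point does not rest on missing cut-offs, however. The article gives this comparison its own list of methods, and that list does not match the stated aim.

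A third reply is that little depends on this. The Discussion treats screening properties as process data useful for further studies, and wide dissemination is tied to acceptance and a positive influence on mental health. A reader might infer that DBED would be promoted as a detection method without a detection rate, or that needless worry about healthy children is the main criticism the Introduction reports. Neither is in the text: the first is speculation, and the Introduction gives two criticisms without ranking them.

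Finally, SDQ is an imperfect reference, so a false positive against it is a disagreement between two screeners and does not show that a concern was unnecessary. That is correct. It limits how the results can be read, but it does not make the listed methods sufficient.

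**Conclusion.** The point holds as a mismatch between a stated secondary objective and the methods listed for it. The methods give association and agreement, which serve the objective in part. They give no sensitivity, specificity or predictive values, and kappa for EWQ against SDQ lacks a common scale. With r = 0.5 and 10% prevalence, sensitivity could lie anywhere from 0.19 to 0.65 depending on the flag rate alone. With kappa at 0.40 it could be 0.40 or 0.90. These values rest on assumed prevalence, correlation and kappa, and on bivariate normality for the first. They show that accuracy is not determined and do not predict the trial's results. The primary analysis and the main between-arm comparisons are unaffected, so this is a change that should be made rather than one the trial depends on.

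**What to change.** In Statistical methods {20a}, under process measures:

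- For parent EWQ, teacher EWQ and DBED concluded concern at baseline, add sensitivity, specificity and predictive values against dichotomised SDQ Total difficulties. State in advance the SDQ cut-off, the SDQ informant (parent or teacher) that defines a positive child, and the rule for a positive EWQ or concluded concern.
- Add ROC curves and AUC for the EWQ totals.
- Give 95% confidence intervals that allow for clustering by kindergarten.
- Use kappa only where both ratings share the same categories, such as parent against teacher EWQ, or reported against concluded EWQ.
- State two limits. Accuracy is relative to SDQ, which the article itself describes as a screening tool, and not to a diagnosis. SDQ is completed 1 to 3 weeks after the conference by raters who know its conclusion, so the apparent accuracy of concluded concern may be inflated.

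The cost is analysis wording only, since EWQ, DBED conclusions and SDQ are already part of the planned data collection. The downside is wide intervals, because EWQ exists only in the intervention arm. The Discussion expects recruitment to exceed the minimum, which would help somewhat. The imprecision should be reported openly.

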### Sample size {14}

The participating children are expected to represent the general population and are not a clinical sample with a presumed high level of mental symptoms. Hence, even if DBED will have a promoting effect on mental health among the children, the difference between the intervention and the control group will probably be small. In the absence of other similar studies, we chose a difference of 0.8 in SDQ Total Difficulties Scale score based on discussions in the project group. Then, we powered the study to be able to detect such a difference between the implementation and the control group. Mplus was used for Monte Carlo simulations assuming the participation of 20 kindergarten (clusters) with ten participating subjects within each cluster and a baseline SDQ mean 5.5 (English norm data: 5.7) SD = 5.5 (σ^2^_within_ = 30.25). The group differences were represented with a predictor of the slope factor in a latent growth curve model. The model assumed normative stability in the controls (mean change = 0.0) and a reduction of −0.8 in the intervention group during the total period. Group sizes were set to be equal. Some between-cluster variation was specified in the intercept factor (σ^2^_between_ = 2.0) to give expected ICC = 0.10 in the six outcome variables over time. The attrition was assumed to be up to 25%. The number of replications was 1000. To achieve the difference of 0.8 with a sample size of *n* = 100 in each group, the statistical power for the testing of group difference was found to be 95%.

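### For parent-teacher agreement on the SDQ, the only summary coefficients named are correlations; no absolute-agreement index is given and no listed method is designated as the agreement result

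*Protocol article*

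**What the plan says.** In the protocol article, Outcomes {12}, one process outcome is "Agreement between parent’s and teacher’s mental health report measured by agreement between parent and teacher SDQ scores", together with the two SDQ impact scores, at baseline and at 12, 24 and 36 months. Section {18a} gives the ranges: 0–40 for the total, 0–10 for each sub-scale, and 0–3 and 0–12 for the two impact scores.

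The methods are in section {20a}, in the block on agreement under process measures. For the SDQ comparison between parents and teachers they are "correlations (Pearson’s and Spearman), CFA, including method factors, LDS models". The item before it, on concern (EWQ) against SDQ, describes what LDS models are for: "Latent difference score (LDS) models will also be explored for common levels and differences within and between families". For parents' and teachers' worries the list is "Cross table with chi-quadrat test, Cohen’s weighted Kappa, CFA, and LDS models".

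The article does not rank the methods within any of these items.

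**The concern.** Parent and teacher rate the same child on the same instrument, so agreement here means giving the same score. A correlation answers a different question: whether the two informants order the children alike. Pearson is unchanged by adding a constant to one informant's scores or multiplying them by a positive constant. Spearman is unchanged by any strictly increasing transformation. If teachers scored every child three points lower, or used half the range, both coefficients would stay where they were.

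Confirmatory factor analysis with method factors separates shared from informant-specific variance. That is useful, but it is not an index of agreement in observed scores. LDS models can estimate a mean difference between informants. That leaves two gaps: no coefficient on the list expresses agreement in level and spread as well as in ordering, and no method is named as the one that decides the matter. At stake is how a process outcome is reported and understood.

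**Working it through.** The article states no figure for parent-teacher agreement, so there is none to reproduce. The check asks how far an absolute-agreement coefficient can fall while the correlation stays fixed, and what the LDS models would recover.

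**Inputs from the article**
- SD 5.5, so s² = 30.25. Sample size {14} assumes "a baseline SDQ mean 5.5 (English norm data: 5.7) SD = 5.5". It is applied here to both informants, which is an assumption.
- n = 200 children, from the abstract: "Parents of at least 100 + 100 children will be recruited".

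**Inputs assumed**
- Parent-teacher correlation r = 0.3, 0.5 or 0.8.
- Constant informant gap d = 0 to 5.5 points.
- Ratio of teacher SD to parent SD, k = 1 or 0.5.

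**1. Equal spreads.** Absolute-agreement ICC = r·s² / (s² + d²/2).

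For r = 0.5:
- d = 2: 15.125 / (30.25 + 2) = 0.47
- d = 3: 15.125 / (30.25 + 4.5) = 0.44
- d = 5.5: 15.125 / (30.25 + 15.125) = 0.33

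Over the range of r:

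| r | d = 0 | d = 1 | d = 2 | d = 3 | d = 5.5 |
|---|---|---|---|---|---|
| 0.3 | 0.30 | 0.30 | 0.28 | 0.26 | 0.20 |
| 0.5 | 0.50 | 0.49 | 0.47 | 0.44 | 0.33 |
| 0.8 | 0.80 | 0.79 | 0.75 | 0.70 | 0.53 |

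A simulation with 200,000 pairs per cell matched these values. Within each row Pearson stayed at r, and Spearman stayed about 0.01 to 0.02 below it, whatever the gap.

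**2. Unequal spreads.** Lin's concordance coefficient = 2·r·k·s² / (s² + k²·s² + d²).
- r = 0.5, k = 0.5, d = 3: 15.125 / (30.25 + 7.5625 + 9) = 15.125 / 46.8125 = 0.32
- r = 1, k = 0.5, d = 3: 30.25 / 46.8125 = 0.65

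The second case is a limiting one. It shows that even a perfect correlation does not guarantee agreement.

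**3. Limits of agreement.** For equal SDs and r = 0.5, the half-width is 1.96 × √(2 × 30.25 × 0.5) = 1.96 × 5.5 = 10.8 points around the mean difference. This describes scatter for individual children. It should not be set against the 0.8-point target in Sample size {14}, which is a difference between group means.

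**4. What an LDS model with a mean structure recovers.** Its mean difference estimates the gap directly; in the simulation a 2-point gap came back as about 2 points in absolute size. With n = 200 and clustering ignored, the standard error is 5.5 × √(2(1 − r)/200):
- r = 0.3: 0.46
- r = 0.5: 0.39
- r = 0.8: 0.25

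At a two-sided 5% level (two-sided is assumed), a 2-point gap would be detected with about 99% power or more, and a 1-point gap with 58% to 98%.

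**The case against.** The strongest reply is that the quoted line names more than correlations. LDS models are on it, and the preceding item says they address differences within and between families. Step 4 shows that a mean structure would expose a gap of 2 points with near certainty. Fitted at each planned time, the models would also show parents and teachers converging or drifting apart. This stands.

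A reader might therefore go too far and infer that the plan judges agreement by correlation alone, that it ignores systematic informant differences, or that it would pass poor agreement off as good. The documents support none of these. They do not say that the correlation carries the conclusion, and the listed methods taken together can reveal a difference in level.

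Two further replies have weight. First, the absence of kappa from this line is weak evidence of an oversight: the EWQ worries have three response categories, where kappa is natural, whereas SDQ totals run from 0 to 40. Only the 0–3 impact score is an obvious candidate. Second, the illustrations rest on assumed values. At r = 0.5 and a 3-point gap the coefficient moves only from 0.50 to 0.44, and few would call 0.50 good agreement to begin with.

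It can also be said that the choice of coefficient belongs in the full protocol or the analysis plan. That reply is only partly persuasive. The article does choose methods for this outcome and places correlations under the heading of agreement, so the comment is on a stated choice and not on missing detail.

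**Conclusion.** The point holds in a limited form. Correlations are listed as agreement measures and are the only summary coefficients for the parent-teacher SDQ comparison. They cannot reflect a difference in level or spread. The LDS models can show the mean difference, but no absolute-agreement index is named and no method is designated as the answer.

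The numerical effect is modest under equal spreads and small gaps: 0.50 to 0.47–0.44 for a 2- to 3-point gap at r = 0.5, and 0.80 to 0.75 for a 2-point gap at r = 0.8. It becomes substantial only with a large gap (0.53 for 5.5 points at r = 0.8) or with unequal spreads (0.32 at r = 0.5). The correlation, the gap and the ratio of spreads are all assumptions; only the SD of 5.5 and the number of children come from the article. This is a minor point on a process outcome and has no bearing on the primary comparison.

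**What to change.** In the SDQ item of the agreement block in section {20a}, designate the agreement result. At baseline and at 12, 24 and 36 months:

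- For SDQ total and sub-scale scores, report the absolute-agreement ICC (or Lin's concordance coefficient) with a 95% confidence interval, and the mean parent-teacher difference with 95% limits of agreement.
- For the 0–3 impact score, report weighted kappa.
- Label Pearson and Spearman as measures of association only.
- Keep CFA with method factors and the LDS models as supporting analyses.

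The cost is a wording change and a few lines of code on data that will be collected anyway. The drawback is that agreement may look lower than the correlation would suggest.
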